**Specific CHF HRQOL**

The specific CHF-related HRQOL will be measured by employing the short form of the Kansas City Cardiomyopathy Questionnaire (KCCQ). The short form of the KCCQ consists of 12 items measured on a 5 or 7-point Likert scale with an overall score of between 0 to 100, with higher scores reflecting better HRQOL(70). This scale has demonstrated high responsiveness, test-retest reliability, and prognostic ability(70).

**Generic HRQOL**

The descriptive system of the Five-dimensional five-level EuroQol (EQ-5D-5L) will be used to evaluate generic HRQOL. The EQ-5D-5L is comprised of five items with five levels. The five items can result in a 5-digit number, which can be adopted to a single utility score by utilizing the Chinese scoring algorithm (71). The EQ-5D-5L has demonstrated good reliability with a Cronbach’s α of 0.857 and validity in the Chinese population (72).

**Secondary outcomes**

The secondary outcomes include measures at the dyadic level and individual level for patients and their caregivers.

**For patients and their family caregivers:**

**Perceived health status**

The EQ-5D-5L visual analog scale (EQ-5D-5L VAS) will be adopted to evaluate the individual’s perceived health status, which is comprised of a single global rating. Potential scores range from 0 to 100, with a higher score reflecting a better perceived health status (71). The reliability of the scale has been demonstrated with a Cronbach’s α of 0.83 among Chinese (73).

**Severity of anxiety**

The Generalized Anxiety Disorder Scale-7 (GAD-7) will be utilized to test the level of severity of anxiety. The GAD-7 consists of 74-point Likert items. The total score ranges from 0 to 21, with lower scores representing anxiety of less severity (74). The GAD-7 has shown good reliability with a Cronbach’s α of 0.91 and construct validity among Chinese (75).

**Severity of depressive symptoms**

The Patient Health Questionnaire (PHQ-9) will be employed to evaluate the level of severity of depressive symptoms. The PHQ-9 covers nine items measured on a four-point Likert scale. The total score ranges from 0 to 27, with lower scores representing less severe depression(76). The Cronbach’s α is 0.91, with good sensitivity and specificity among Chinese (75).

**Perceived quality of the relationship**

The short form of the Dyadic Adjustment Scale (DAS-7) will be adopted to examine the perceived quality of the relationship between the patients and their caregivers. The DAS-7 consists of 7 items measured on a 6 or 7-point Likert scale. The total score ranges from 0 to 36, with a higher score indicating a higher-quality relationship. It was used among CHF patients and caregivers and found to have acceptable Cronbach's α coefficients of 0.70-0.78 (77).

**Perspective-taking** **ability**

The most widely used scale to measure perspective-taking ability is the subscale on perspective-taking in the Interpersonal Reactivity Index (IRI) (78). The Chinese version of the IRI includes a 5-item subscale on perspective taking, measured on a 5-point Likert scale. The Cronbach's α coefficient of the perspective-taking subscale is 0.767 among Chinese (79).

- S**elf-compassion**

The short form of the Self-compassion scale (SCS–SF), which is comprised of 12 items, will be utilized to measure self-compassion (80). The Chinese version of SCS–SF demonstrated acceptable reliability, with a Cronbach’s α of 0.686, and validity among Chinese (81).

**Psychological flexibility**

The Comprehensive Assessment of Acceptance and Commitment Therapy Processes (CompACT) (82) will be utilized to evaluate the psychological flexibility of individuals. The Chinese version of CompACT consists of 18 items measured on a 7-point Likert scale. Scores range from 0 to 126, with a lower score representing a greater level of psychological flexibility. With a Cronbach's α of 0.87, the validity and reliability of CompACT have been demonstrated in a non-clinical sample in China (83).

**Patient-only outcomes:**

**Health service utilization**

The frequency of all course and cardiac-related readmissions and emergency department visits in any hospital will be assessed by self-reports.

**CHF self-care behavior**

The CHF self-care behavior of patients will be evaluated using the European Heart Failure Self-care Behavior Scale (EHFScBs) and self-reported smoking and alcohol drinking status. The ECHFScBs is comprised of 12 items measured on a 5-point Likert scale, and is used to evaluate CHF self-care behavior, with an emphasis on help-seeking and regimen-complying behavior(84). The possible total score ranges from 12 to 60, with a higher score indicating a lower level of self-care performance. The Chinese version of the ECHFScBs demonstrated good reliability, with a Cronbach’s α of 0.82, and validity among Chinese patients with CHF(85). As smoking and drinking behavior were excluded from the EHFScBs, patients will be asked to report their smoking and drinking status.

**Caregiver-only outcome:**

**Perceived caregiving burden**

The Zarit Caregiver Burden Interview (ZBI) will be used to evaluate feelings of caregiving burden (86). It consists of 22 statements measured on a 5-point Likert scale, with a total score ranging from 0 to 88. The Chinese version has shown good internal consistency (Cronbach's α 0.875) among Chinese caregivers and good validity(87).

# Procedure

Potential CHF patients will be initially identified by the staff nurses through reviewing electronic medical records. The staff nurses will contact the designated contact persons of the patients via telephone to obtain contact information of patients and their FCs. Then, both the patients and their FCs will be approached by phone and will be provided with an introduction to the study's purpose and procedure. If one member of patient-caregiver dyads is unable to participate, they will be required to phone back to inform the research team. If there are no response, the staff nurse will follow up with a phone call to provide further information on the study. Interested patient-caregiver dyads will be invited by the staff nurse to attend either through an online assessment via WeChat or through an in-person clinical visit to confirm eligibility.

After the eligibility of the patient and the patient’s FC is confirmed, the staff nurses at the Department of Cardiology will provide a detailed explanation of the study’s aim, methods, potential benefits, and risks, including all necessary elements of informed consent, either in the patient’s regular clinic or online via a WeChat video call. Once oral consent is given, the patient-FC dyads will receive a link to the information sheet via the WeChat platform. Verbally recorded informed consent will be sought from each CHF patient and their FC within one week after documents have been sent out over the smartphone.

Technical support before and during the sessions will be provided. Prior to the sessions, a video that shares step-by-step instructions on how to log onto VooV Meeting via a WeChat mini program will be provided to each dyad. Research assistants will conduct brief tutorials, either in person in the clinic or online via smartphone with dyads in the lead up to the first session to help them set up VooV meetings via the WeChat mini program. This is to ensure they are able to access group sessions and check their audio and video connections during the sessions. Throughout the program, research assistants will also provide timely online support on technical issues for the patient-FC dyads.

To promote recruitment and retention, the dyad will be given an incentive to undergo each assessment during the study, as compensation for their time; for example, each participating dyad will receive one set of CHF self-care materials for the baseline assessment, 50 Yuan RMB (≈6.97 USD) for each session, 50 Yuan RMB (≈6.97 USD) for the post-intervention assessments while 100 Yuan RMB (≈ 13.95 USD) for the 3-month follow-up assessment. The monetary incentives will be sent to the family via the WeChat platform. The material will be sent directly to the family by post.

A detailed schedule and timing of the evaluations are presented below in Table 2. T5 and T6 represent the time immediately post-intervention and at the 3-month follow-up point, respectively.

# Data management

A detailed database will be established to record the assessments and progress of each participant. Each participant will assign a unique identifier to preserve their confidentiality. This database will be password-protected and only accessible to authorized members of the research team. The researcher coordinator will monitor the data collection process, quality, and safety periodically. Any adverse events will be identified, documented, and handled with the caution. In cases of discrepancies, the research team including experts in cardiologist, nurses, and academia, will discuss and reach a consensus. Consultation with clinical trials specialists in the study hospital will be sought if required.

# Statistical analysis

All quantitative data collected from the participants will be numerical coded, and analyzed utilizing IBM SPSS 27. Baseline sociodemographic and clinical data will be used using medians, proportions, and counts for categorical data; while means, standard deviations (SDs), skewness, and kurtosis will be used for continuous variables for participants in two groups. Differences in the participants’ characteristics at baseline will be explored using an independent T-test or Mann-Whitney U test for continuous variables, and Chi-squared or Fisher’s Exact test for categorical variables. The primary outcome and secondary outcomes will be summarized using means with SDs for the ACT group and CE groups. Randomized testing at baseline between the study groups will be performed to identify potential covariates. The differences in these outcomes between the ACT group and the CE groups over time will be analyzed using generalized estimating equations (GEE) which account for missing data at random. If any covariance is detected in the baseline comparison, it will be adjusted in the analysis of the effects of the intervention. Subgroup analysis will be adopted for specific factors (e.g., intervention completion and non-completion). The level of statistical significance is predetermined at p<0.05 (two-tailed). The intention to treat principle will be applied by comparing the ACT group with CE groups as randomized despite adherence to the intervention. Cohen’s d will be calculated to estimate effect sizes of between-group comparisons.

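### Means with SDs, and Cohen's d as the only named effect size, do not suit the readmission and emergency-visit counts or smoking and drinking status (minor)

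*Protocol*

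**What the plan says.** The Statistical analysis section of the Protocol gives one summary rule for outcomes: "The primary outcome and secondary outcomes will be summarized using means with SDs for the ACT group and CE groups". It names one effect measure: "Cohen’s d will be calculated to estimate effect sizes of between-group comparisons". Differences between groups over time "will be analyzed using generalized estimating equations (GEE) which account for missing data at random"; no distribution or link is stated.

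The same section does distinguish data types for baseline characteristics, where it plans "medians, proportions, and counts for categorical data" and lists Chi-squared or Fisher's exact tests. That distinction is not carried over to the outcomes.

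Under Secondary outcomes the Protocol says "The secondary outcomes include measures at the dyadic level and individual level for patients and their caregivers". Two of the patient-only entries are not scale scores:

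- Under the Health service utilization heading: "The frequency of all course and cardiac-related readmissions and emergency department visits in any hospital will be assessed by self-reports".
- Under the CHF self-care behavior heading, in addition to the scale score: "patients will be asked to report their smoking and drinking status".

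**The concern.** The outcome rule suits the questionnaire scores, which make up most of the list. It does not suit the two entries above. Smoking or drinking status is a category, and a mean with SD has no natural meaning for it unless it is coded 0/1, in which case the proportion is the plain way to report it. Readmissions and emergency visits are counts that are likely to be zero for most patients over weeks to months. The SD then exceeds the mean, and Cohen's d depends on the background event rate and the dispersion as well as on the treatment effect.

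The practical risk is in how the results are read. The sample size rests on a standardized effect of 0.50, so readers have a ready yardstick for any d in the report. A reduction in admissions that is sizeable in relative terms could look negligible against it.

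This differs from a detail left to the SAP. The Protocol states a rule. An SAP that follows it inherits the misfit, and one that departs from it disagrees with the Protocol.

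**Working it through.** **The plan's own figure.** The Protocol attaches no number to this point. Its sample size reproduces: a two-sample t-test with d = 0.50, two-sided alpha 0.05 and power 0.80 needs 63.77, so 64 per arm and 128 in total; 128 / (1 − 0.20) = 160 dyads. Nothing below depends on it.

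**Rule against outcome type.**

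| Secondary outcome | Type | Stated summary | Fit |
| --- | --- | --- | --- |
| Questionnaire scores | Scale score | Mean, SD | Suitable |
| Readmissions, emergency visits | Count | Mean, SD | Mean readable as a crude rate; SD and d poor |
| Smoking, drinking status | Category | Mean, SD | Unsuitable |

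**Counts: illustration under assumed rates.** The Protocol gives no event rates. Assume a control mean m1 of 0.1, 0.2 or 0.3 events per patient and a rate ratio of 2/3, so m2 = (2/3) × m1. Let the variance be m + a·m², with a = 0 (Poisson) or a = 2 (negative binomial).

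- Share of controls with no event: exp(−m1) for Poisson; (1 + a·m1)^(−1/a) for negative binomial.
- d = (m1 − m2) / √[(var1 + var2)/2].

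| m1 | m2 | No event, a = 0 / a = 2 | Control SD, a = 0 / a = 2 | d, a = 0 / a = 2 |
| --- | --- | --- | --- | --- |
| 0.1 | 0.067 | 0.90 / 0.91 | 0.32 / 0.35 | 0.12 / 0.11 |
| 0.2 | 0.133 | 0.82 / 0.85 | 0.45 / 0.53 | 0.16 / 0.14 |
| 0.3 | 0.2 | 0.74 / 0.79 | 0.55 / 0.69 | 0.20 / 0.16 |

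Last row worked out:

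- Poisson: (0.3 − 0.2) / √[(0.3 + 0.2)/2] = 0.1/√0.25 = 0.20.
- a = 2: the variances are 0.3 + 2 × 0.09 = 0.48 and 0.2 + 2 × 0.04 = 0.28, so d = 0.1/√0.38 = 0.16.

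In every row the SD exceeds the mean, so mean minus one SD is negative. The same one-third reduction gives d anywhere from about 0.11 to 0.20, with only the assumed rate and dispersion changing.

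**Status: illustration under assumed proportions.** With d = (p1 − p2) / √[(p1(1 − p1) + p2(1 − p2))/2]:

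- 30% vs 20%: 0.10/√[(0.21 + 0.16)/2] = 0.10/0.430 = 0.23; odds ratio (0.20/0.80)/(0.30/0.70) = 0.58.
- 20% vs 10%: 0.10/√[(0.16 + 0.09)/2] = 0.10/0.354 = 0.28.
- 50% vs 40%: 0.10/√[(0.25 + 0.24)/2] = 0.10/0.495 = 0.20.

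The same 10-point difference gives d of 0.20 to 0.28 according to the background proportion.

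**The case against.** The strongest reply is that this is loose drafting in one descriptive sentence. The baseline plan shows that the team distinguishes variable types. A mean number of admissions per patient is a readable crude rate, and a 0/1 mean is a proportion. A small d for a fall from 0.10 to 0.067 admissions is not false, because the absolute change is small. For smoking at 30% vs 20%, the usual logistic conversion of the odds ratio, |ln 0.583| × √3/π, gives about 0.30 against d = 0.23; both would be called small.

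Most of that stands, and it limits the severity. It does not remove the misfit: the sentence covers the secondary outcomes without exception, and the SD and d remain poor summaries for these variables.

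A reader might infer more than the text supports:

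- **That Cohen's d is prescribed for every secondary outcome.** The sentence on d is general and lists no outcomes. What can be said is that d is the only effect size named.
- **That the tests are invalid, or that symmetric normal-theory intervals will be put on sparse counts.** The Protocol states no interval method. GEE can fit count and binary outcomes, and the link may properly be left to the SAP.
- **That raw counts mix windows of about one and three months.** Assessments fall after four weekly sessions and again three months later, and sessions are suspended during hospitalization (Eligibility), but no recall period is given for the counts. Unequal windows are therefore only a possibility. If scheduled windows were the same in both arms, unequal length would produce a shared time effect and not, by itself, a group difference.

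**Conclusion.** The point holds as a minor one. The stated summary rule does not fit the smoking and drinking categories. For readmissions and emergency visits, the SD and Cohen's d describe sparse counts poorly. Smoking and drinking status is the clearest case.

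The sizes rest on assumed rates, because the Protocol supplies none, and they illustrate the problem without predicting the trial's results. Description and effect size for a few secondary outcomes are affected. The primary quality-of-life scores, the sample size and the validity of the GEE tests are not.

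**What to change.** In the Statistical analysis section, limit means with SDs and Cohen's d to the scale scores, and add two sentences:

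- **Readmissions and emergency visits:** report the number of events, the number of patients with at least one event, and a rate ratio with 95% CI from the planned GEE with a count distribution and log link. State the recall window, and include the log of observed time as offset if windows differ.
- **Smoking and drinking status:** report n (%) by group, with an odds ratio or risk difference and 95% CI from the planned GEE with a binary distribution.

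The cost is about one paragraph of wording. The GEE procedure in the named software supports these distributions, and no new outcome measure or change of model family is needed.

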## A prior power analysis was performed to estimate the sample size needed in this study using G*Power. Previous studies in CHF have shown that mean differences in HRQOL between patients who received a psychosocial intervention and the usual care ranged from 0.11 to 0.68 (42). For ACT interventions targeting HRQOL, a recent review meta-analysis reported a mean effect of 0.48 for the clinical and non-clinical population, ranging from 0.37 to 1.55 when those who received the ACT intervention were compared to the active control, not including CBT (43). Thus, an estimated effect size of 0.50 was adopted across the above reviews. Targeting that effect size at a power of 0.8 with a prior power calculation, a minimal sample size of 128 is required to detect the difference between the ACT group and CE groups. Considering a weighted dropout rate of 16% for those participating in an ACT intervention indicated in a recent meta-analysis (44), and given group-setting and patient-caregiver dyadic participant requirements for the interventions, the total sample size was increased to 160 patient-FC dyads, accounting for an anticipated dropout rate of 20%.

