# Randomization and blinding

## In this study, allocations with a ratio of 1:1 will be performed through an online randomization program (<https://www.randomizer.org/>) by an independent researcher, who will be excluded from any other activity throughout the intervention. The unit of randomization is the patient-FC dyad. The randomization list will be stratified by the type of relationship between the patients and caregivers (e.g., spousal relationship vs. non-spousal relationship) with a block size of 4 or 6. The allocation sequence will be printed and sealed separately in opaque envelopes by the randomizer.

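### Covariates are to be picked by baseline significance tests, so the adjustment set depends on chance and precision is given up that a fixed set would secure

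*Protocol*

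**What the plan says.** The protocol's Statistical analysis section first has the two groups' baseline characteristics compared by t-test or Mann-Whitney test, or by chi-squared or Fisher's exact test. It then gives these comparisons a purpose: "Randomized testing at baseline between the study groups will be performed to identify potential covariates". The consequence follows: "If any covariance is detected in the baseline comparison, it will be adjusted in the analysis of the effects of the intervention". Here covariance can only sensibly mean an imbalance or a covariate showing one. Outcomes are compared between arms over time by GEE. No covariate is named for that model, and the role of the baseline score is not stated.

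Under Randomization and blinding, "The randomization list will be stratified by the type of relationship between the patients and caregivers", that is, spousal against non-spousal, in blocks of 4 or 6. The Statistical analysis section does not mention this factor.

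Under Sample size calculation, "an estimated effect size of 0.50 was adopted across the above reviews" and "a minimal sample size of 128 is required to detect the difference between the ACT group and CE groups" at a power of 0.8. This is raised to 160 dyads for 20% dropout.

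**The concern.** Allocation is by a random list in sealed envelopes, opened after the baseline assessment. If that works as described, any baseline difference between arms is chance, and a significance test on it asks a question whose answer is already known. What makes a covariate worth adjusting for is how strongly it predicts the outcome, and the test does not measure that. The rule can admit a variable that predicts nothing and leave out a strong predictor that happens to be balanced.

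Two variables matter most. The stratification factor is balanced by the blocking, so a test of imbalance is the wrong device for bringing it in. The baseline value of each outcome is likely to be the strongest single predictor, yet it would enter as a covariate only if it happened to differ significantly between arms, and only if baseline scores are among the variables tested, which the text leaves open.

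At stake are the precision of the primary comparisons and knowing the primary model in advance.

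**Working it through.** **Inputs.** From the protocol: standardised effect 0.50, two-sided 5% level, power 0.8, 128 evaluable (64 per arm), 20% dropout, 160 dyads, blocks of 4 or 6 within relationship type. Assumed, because the protocol does not give them: baseline/follow-up correlation r of 0.3 to 0.7; the 0.50 scaled to the SD of the follow-up score; and, for the simulations, 60% spousal dyads.

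**1. The plan's own figures.** A two-sample t-test without covariates (noncentral t) at d = 0.50 has power 0.795 with 63 per arm and 0.801 with 64 per arm. Hence 128, and 128 / (1 − 0.20) = 160. Both figures reproduce.

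**2. How often chance supplies a covariate.** For k independent tests at 5%, P(at least one flag) = 1 − 0.95^k.
- k = 10: 0.40
- k = 13: 0.49
- k = 14: 0.51
- k = 20: 0.64

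The examples in the Outcomes section come to about 14 if age, gender, education and employment are counted for both dyad members (8), plus relationship (1) and five clinical items. Without relationship, which is balanced by design, the count is 13.

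**3. Whether the stratification factor could be flagged.** In 20,000 simulated stratified block randomisations of 160 dyads, a chi-squared test on relationship type was never significant. The smallest p-value was 0.67.

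**4. Value of always adjusting for baseline.** Relative variance of the treatment contrast:
- follow-up score alone: 1
- baseline-adjusted: 1 − r²
- change from baseline: 2(1 − r)

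Power is that of the t-test with 64 per arm at 0.50 / √(relative variance).

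| r | Follow-up only | Baseline-adjusted | Change contrast |
|---|---|---|---|
| 0.3 | 0.80 | 0.84 | 0.66 |
| 0.5 | 0.80 | 0.90 | 0.80 |
| 0.7 | 0.80 | 0.98 | 0.95 |

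Example at r = 0.5: 0.50 / √0.75 = 0.577, power 0.90. Equivalently, 128 / 0.75 = 171, so 128 adjusted participants carry the information of 171 unadjusted ones.

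The last column applies only if the GEE takes baseline as a response and tests the group difference in change. The protocol does not say that it does.

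**5. The rule itself, simulated.** There were 8,000 trials per scenario, with one outcome, one follow-up time, 64 per arm, a stratum/outcome correlation of 0.2, and baseline independent of stratum. The rule adjusts for baseline only if its test is significant.

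| r | Power, rule | Power, baseline and stratum fixed | Type I error, rule | Type I error, fixed |
|---|---|---|---|---|
| 0.5 | 80.9% | 91.2% | 3.9% | 4.9% |
| 0.6 | 82.2% | 95.0% | 3.5% | 4.6% |
| 0.7 | 82.2% | 98.4% | 3.0% | 5.2% |

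The rule is conservative because, whenever baseline is not flagged, the standard error still carries outcome variation that baseline would have explained.

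**The case against.** The strongest reply is that little is lost against the plan. The sample size assumes no adjustment, an unadjusted follow-up comparison still has about 0.80 power, and the simulated rule keeps 81% to 82%. This stands: the cost is mainly a gain forgone.

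Second, the text says that detected imbalances will be adjusted for, not that nothing else will be, and a separate analysis plan may list fixed covariates. This stands in part. It rules out saying that the stratification factor can never enter the model. It does not remove the point, because the protocol states testing as the way covariates are identified, and that stated rule is what needs changing.

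Third, the 40% to 64% range assumes independent tests, while patient and caregiver characteristics are probably correlated. Adjusting for one irrelevant variable also costs only about one degree of freedom. Both are fair: the figure shows how arbitrary the selection is, not how much harm it does.

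Three stronger readings are tempting and not supported:

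- A reader might infer that the trial falls below its planned power because the GEE tests change from baseline. The protocol names no contrast and no role for baseline. It also does not say whether 0.50 is scaled to the follow-up or the change SD; if it is the change SD, a change analysis has 0.80 power at any correlation.
- A reader might add the loss from a follow-up-only model to the loss from a change model. These are alternative readings, and only one can apply.
- A reader might see outcome-driven model selection that inflates false positives. The rule looks at baseline data only, and the simulated type I error is below 5%.

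**Conclusion.** The point holds as a flaw in a stated rule. Selecting covariates by baseline tests makes the adjustment set a matter of chance, would in practice pass over the factor the randomisation is stratified on, and uses the baseline score as a covariate only by accident.

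If the 0.50 is on the follow-up SD and 128 are evaluable, the forgone power against always adjusting for baseline is about 4, 10 and 18 percentage points at correlations of 0.3, 0.5 and 0.7 (0.84, 0.90 and 0.98 less 0.80). If the GEE instead tests change, the gap is about 18, 10 and 3 points (0.84 − 0.66, 0.90 − 0.80, 0.98 − 0.95), and power is under 0.80 only for correlations below about 0.5. Both sets depend on a correlation the protocol does not give. The trial remains valid, and inference under the rule errs on the cautious side. The change should be made because it recovers precision and fixes the model in advance at almost no cost.

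**What to change.** In the Statistical analysis section, delete the sentence that uses baseline testing to find covariates and the sentence that adjusts for what is detected. In their place, state that the GEE for each outcome contains treatment, visit, treatment-by-visit, the baseline value of that outcome, and relationship type (spousal or non-spousal) as fixed terms, with follow-up scores as the response. List any further prognostic covariates by name before the data are examined. Report baseline characteristics by arm descriptively, without p-values.

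The cost is a change of wording. The baseline scores and relationship type are already collected, and no dyads are added. Adding NYHA class for patients is optional and not needed to resolve this point.

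### The protocol credits GEE with handling data missing at random, a property that unweighted GEE does not have in general; the resulting bias could be nil or material, depending on choices the protocol leaves open

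*Protocol*

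**What the plan says.** The Statistical analysis section of the protocol names one method for the primary and secondary outcomes: differences between the arms over time "will be analyzed using generalized estimating equations (GEE) which account for missing data at random". It also commits to an intention-to-treat comparison. It names no working correlation.

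Under Outcomes, assessments are at baseline, directly after the intervention and 3 months later. Participants who stop the intervention are to be encouraged to stay in the assessments. The Objectives place the comparison at the 3-month follow-up.

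The sample size paragraph starts from "Considering a weighted dropout rate of 16% for those participating in an ACT intervention" and then reports that "the total sample size was increased to 160 patient-FC dyads, accounting for an anticipated dropout rate of 20" per cent.

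**The concern.** Missing at random is a technical term: the chance of being missing may depend on anything already observed, including earlier outcome scores. Ordinary GEE uses every available record, but its estimating equations are guaranteed unbiased only under the narrower conditions of data missing completely at random, or missing in a way that depends only on covariates in the model. Validity under missing at random has to be added by weighting or imputation, or comes with a correctly specified likelihood model.

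The design makes the distinction relevant. The post-intervention score is collected before the 3-month visit, so people who did poorly after the sessions could be lost afterwards in a way that their recorded data would explain. If that happens differently in the two arms, unweighted GEE can misstate the 3-month difference although the information needed to correct it is in the database. The sentence also tells whoever writes the detailed analysis that nothing more is needed.

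**Working it through.** **Step 1. The plan's own figures.** Inputs from the sample size paragraph and the Statistical analysis section: standardised effect 0.50, power 0.80, two-sided 5% level, 1:1 allocation. The two-sample t-test (noncentral t) needs 63.77 per arm, rounded up to 64, so 128 in total; power at 64 per arm is 0.801. Allowing for dropout, 128 / (1 − 0.20) = 160. Both stated figures reproduce.

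**Step 2. The bias by formula, independence working correlation.** With separate means for each arm and visit, independence GEE estimates an arm's 3-month mean by the mean of those still observed. Take equal variances (SD 1), correlation ρ between the post-intervention and 3-month scores, and dropout before the 3-month visit depending only on the post-intervention score. Then

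bias in the difference = ρ × (m_ACT − m_CE),

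where m is how far the mean post-intervention score of those retained lies above that of everyone in the arm. With z the deviation from the arm mean and dropout probability p(z) = 1 / (1 + exp(z − a)),

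m = E[z(1 − p(z))] / E[1 − p(z)],

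with a set to give the chosen dropout rate. The dropout odds thus rise e¹ = 2.7-fold per SD lower score. Numerical integration gives m = 0.091 at 10% dropout, 0.133 at 15%, 0.173 at 20%, 0.213 at 25% and 0.253 at 30%.

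- 20% in each arm, score-dependent in ACT, random in control: 0.5 × 0.173 = 0.087 for ρ = 0.5; 0.7 × 0.173 = 0.121 for ρ = 0.7. Estimates are 0.59 and 0.62 against a true 0.50.
- 10% control, 30% ACT, same slope, ρ = 0.6: 0.6 × (0.253 − 0.091) = 0.097, estimate 0.60.
- 15% control, 25% ACT, ρ = 0.6: 0.6 × (0.213 − 0.133) = 0.048, estimate 0.55.
- Same slope and same rate in both arms: m_ACT = m_CE, so the bias is 0.

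**Step 3. Other working correlations, by simulation.** 400,000 dyads, three visits, correlations 0.5 to 0.6, true 3-month effect 0.50, 20% missing overall at 3 months, slope 1 on the post-intervention score. Entries are estimates of 0.50; the last column is inverse-probability-weighted GEE using the true dropout probabilities.

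| SD by visit | Dropout control / ACT | Independence | Exchangeable | AR(1) | Unstructured | Weighted |
|---|---|---|---|---|---|---|
| equal | 20% / 20%, same mechanism | 0.498 | 0.499 | 0.499 | 0.499 | 0.497 |
| equal | 15% / 25% | 0.546 | 0.501 | 0.499 | 0.501 | 0.496 |
| equal | 10% / 30% | 0.592 | 0.501 | 0.498 | 0.502 | 0.494 |
| 0.8, 1, 1.4 | 20% / 20%, same mechanism | 0.495 | 0.496 | 0.496 | 0.496 | 0.494 |
| 0.8, 1, 1.4 | 15% / 25% | 0.571 | 0.531 | 0.528 | 0.516 | 0.500 |
| 0.8, 1, 1.4 | 10% / 30% | 0.637 | 0.555 | 0.550 | 0.524 | 0.507 |

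With equal variances, modelling the correlation removes nearly all the bias. With rising variances some remains, because a single common scale does not describe the data even when the correlation is unstructured. In an extreme case, with opposite dropout directions in the two arms and rising variances, the range is 0.39 to 0.61 for exchangeable or AR(1) and 0.45 to 0.55 for unstructured. The direction can reverse: with equal variances, 30% dropout in control and 10% in ACT gave 0.40 under independence.

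**Step 4. Type I error, independence GEE, 160 dyads, 4,000 replicates, equal variances, nominal 0.05.** Completely random 0.051; same mechanism in both arms 0.051; 15% / 25% 0.067; 10% / 30% 0.088; opposite mechanisms 0.215.

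**The case against.** The strongest reply is that the larger figures come from one working correlation that the protocol never chose. In the scenario with score-dependent dropout in ACT only, ordinary GEE with an exchangeable or unstructured working correlation gives 0.50 to 0.51, without weighting or imputation. That stands. A reader might infer that the primary result will be inflated by 17% to 24% (0.087/0.50 and 0.121/0.50). The documents do not support this, because it needs both an independence working correlation and one-sided dropout, and the protocol states neither.

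The reply can also point to the symmetry of the arms: the Interventions section gives both four weekly two-hour online sessions, and the Procedure section describes the same payments for every dyad. The content does differ (experiential ACT work against didactic teaching), so arm-specific loss is possible, but nothing shows that it will occur.

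Nor does the planning figure forecast a fifth of 3-month outcomes missing. It is built on dropout among people taking part in ACT interventions, assessment after stopping is encouraged, and the 3-month assessment pays twice the post-intervention one (100 against 50 Yuan). Fewer missing outcomes would mean less bias, but would not make the missingness completely random.

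Finally, a reader might conclude that no step for missing data is planned. That cannot be said: working correlation, imputation and weighting are often left to a statistical analysis plan, and none is at hand. What survives is narrower. The protocol does not stay silent; it asserts a property that the named method lacks in general, and a later document that adds a method would leave that assertion wrong.

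**Conclusion.** The sentence is an error about the primary analysis and should be fixed. Its consequence is conditional. For a true effect of 0.50 SD with 20% of 3-month outcomes missing, the bias runs from about zero (same dropout slope and rate in both arms, or working correlation and variance close to correct) to 0.09 to 0.12 SD (independence, score-dependent dropout in ACT only). Exchangeable or unstructured GEE lies between, at 0.024 to 0.055 SD, with 10% versus 30% dropout and SDs rising from 0.8 to 1.4.

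The correlations, variances, dropout slopes and rates by arm are assumptions, as is placing all the loss after the post-intervention visit. Harsher assumptions, such as opposite dropout directions in the two arms, give larger bias, but nothing in the protocol points to them. That the claim is wrong in general needs none of these assumptions.

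**What to change.** Delete the claim, state the assumption that unweighted GEE needs, and make the primary analysis valid under missing at random in one of these ways:

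- keep GEE, applied after multiple imputation that includes arm, baseline and post-intervention scores;
- keep GEE with inverse-probability weights from a model for remaining in assessment, given arm and earlier scores;
- use a likelihood-based mixed model for repeated measures with arm-by-visit means and an unstructured within-person covariance.

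If GEE is kept, name the working correlation. GEE need not be abandoned; its robust standard errors are a fair reason to keep it for bounded scales such as the EQ-5D-5L utility. A sensitivity analysis for departures from missing at random would complete the change. The choice should be made before outcomes are seen by arm.

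The cost is a change of wording and somewhat more analysis work. No extra data are needed and the target stays at 160 dyads. Each option brings its own reliance on a correctly specified imputation, weight or covariance model.
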